### **7.3 Time to Progression (TTP)**

Patients potentially eligible for this study will be followed from the time of their initial presentation, if possible. The TTP will be defined radiographically or clinically, as delineated above; or alternatively defined by a significant overall change in clinical status as assessed by the study neuro-oncologist, [name]. or his designate. In the absence of radiographic or histologic evidence of progression, clinical progression will be defined as a change in KPS of  $>30$  points or a change in MMSE of  $>6$  points that is not reversible with medical therapy within 2 months. Clinical progression in this context will constitute a DLT if not attributable to a concomitant medication, co-morbid event, or disease progression that has been documented radiographically or clinically.

An intent-to-treat analysis will be conducted to compare the TTP experience of patients identified to receive vaccine treatment upon completion of concurrent external beam radiation and temozolomide assuming there was no intervening disease progression to that experienced by a historical cohort of patients administered the same external beam radiation and temozolomide treatments(Stupp, Mason et al. 2005). Of particular interest is whether the TTP experience of the two groups begins to diverge at the time that vaccine is administered 3-4 months after patient enrollment.

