The Stupp regimen of adjuvant and maintenance radiation and temozolomide is generally considered the standard of care for newly diagnosed resectable GBM(Stupp, Mason et al. 2005). It is notable, however, that the Stupp study had relatively poor compliance with the maintenance temozolomide. On the combined chemoradiation arm, only 78% of patients started maintenance temozolomide, and only 47% of patients completed all 6 cycles. The most frequent reason for early termination was disease progression(Stupp, Mason et al. 2005). It is unclear, therefore, what clinical benefit the maintenance regimen added. This question is currently being studied in separate trials.

This protocol will call a slight delay in the initiation of the second cycle of maintenance chemotherapy in all arms. Considering the very limited dose density of maintenance temozolomide actually given in the Stupp study, it is very unlikely that these delays of 1-3 weeks will significantly compromise clinical outcome.

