## 5 INVESTIGATIONAL PLAN

### 5.1 Preparation and Administration of Therapeutic Agents

#### 5.1.1 Overview

Twenty patients with newly-diagnosed EGFRvIII+ high grade glioma will undergo leukapheresis for immunologic monitoring. Only 1 dose level of daclizumab (1 mg/kg) will be assessed. The decision to dose escalate in subsequent trials will be dependent on analysis of the safety and immunologic responses obtained in this trial. Patients will be followed until death. This study will be halted if any 2 patients experience a drug-related Grade IV or irreversible Grade III toxicity. After initial leukapheresis, all patients will then receive RT and concurrent TMZ at a standard targeted dose of 75 mg/m^2/d. Patients with progressive disease during radiation, dependent on steroid supplements above physiologic levels at time of vaccination, unable to tolerate TMZ or whose PBLs fail to meet release criteria will be replaced, but no more than 40 patients will be enrolled overall. Remaining patients will then receive the initial cycle of TMZ at a targeted dose of 100mg/m^2/d for 21 days 3 ± 1 weeks after completing RT and will be independently randomized to receive daclizumab versus saline simultaneous with vaccine #1. An additional cohort of 6 patients (cohort #2) will receive serial administrations of daclizumab during vaccine # 1, vaccine # 3, and during the recovery from each TMZ cycle for the first 3 cycles at the same dose. Vaccines will be given intradermally and divided equally to both inguinal regions. The calculated dosage of daclizumab will be administered in a 50 mL of sterile 0.9% sodium chloride solution via a peripheral or central vein over a 15 minute period. Vaccine #2 and #3 will occur at 2 week intervals. Patients will then be treated monthly with TMZ cycles for a total of 6 cycles after RT. TMZ will be given on days 1-21 of a 28 day cycle. While standard dose 21-day TMZ treatment at 100 mg/m^2/day is recommended, the TMZ regimen may be adjusted at the discretion of the treating neuro-oncologist. Vaccine will always be given on day 21 ± 2 of each 28 day TMZ cycle. Subsequent vaccines will be given on day 21 ± 2 of each of the 5 remaining TMZ cycles. Cohort #2 will receive subsequent vaccinations along with daclizumab (1 mg/Kg) on day 21± 2 for first 3 cycles. Vaccines will then continue monthly until progression. An additional leukapheresis will be required for any patients who have a positive DTH skin test for PEPvIII for immunologic monitoring. Patients will be imaged after vaccine #4 and then bimonthly without receiving any other prescribed antitumor therapy until progression. Blood work for immunologic monitoring will be drawn before vaccine #1 and then monthly after vaccine #3. Blood work for sub-clinical autoimmunity will be drawn before vaccine #1 and every 4 months after vaccine #3. As part of standard care for these patients, upon tumor progression, participants may undergo stereotactic biopsy or resection. As this is not a research procedure consent will be obtained separately. However, if tissue is obtained, it will be used to confirm tumor progression histologically and to assess immunologic cell infiltration and EGFRvIII antigen escape at the tumor site.

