Patients will receive TMZ which will be delivered every 4 weeks. Therefore, in addition to the concurrent TMZ (75 mg/m^2/d) given with radiation, a total of 6 additional cycles of TMZ (100 mg/m^2/days 1-21) will be given. While standard dose 21-day TMZ treatment at a target dose of 100 mg/m^2/day is recommended, TMZ regimen may be adjusted at the discretion of the treating neuro-oncologist. Vaccine will always be given on day  $21 \pm 2$  of each 28 day TMZ cycle. Subsequent vaccines will be given on day  $21 \pm 2$  of each of the five remaining TMZ cycles. Cohort #2 will receive subsequent vaccinations along with daclizumab (1 mg/Kg) on day  $21 \pm 2$  for first 3 cycles. Vaccines will then continue monthly until progression. An additional leukapheresis will be required for any patients who have a positive DTH skin test for PEPvIII for immunologic monitoring.

If the TMZ cycles are completed without progression, monitoring will continue until clinical or radiographic progression without any additional prescribed antitumor therapy. During that time period, patients will be monitored clinically with routine physical and neurologic examinations and MMSE testing at every visit and with a contrasted-enhanced CT or MRI every  $8 \pm 4$  weeks. Peripheral blood will be obtained as outlined in the study flow sheet below for sub-clinical autoimmunity and immunologic monitoring.

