### **7.4 Survival**

Survival data in the context of this Phase I/II trial will be interpreted with great care. Still there are a few studies in the literature that may be able to be compared to our study to some degree given that they have similar patient populations. For example, the carmustine polymer study(Westphal, Hilt et al. 2003) and the TMZ study(Stupp, Mason et al. 2005), both have a set of very similar inclusion and eligibility criteria.

In addition, the authors of this study are also aware of the benefit of recursive partitioning analysis of prognostic factors in the comparison of different treatment strategies for patients with MG(Curran, Scott et al. 1993; Lamborn, Chang et al. 2004). Comparison with these studies will allow us to compare the results of the current clinical trial to previously published trials of patients with similar prognostic features.

An intent-to-treat analysis will be conducted to compare the survival experience of patients identified to receive vaccine treatment upon completion of concurrent external beam radiation and temozolomide assuming there was no intervening disease progression to that experienced by a historical cohort of patients administered the same external beam radiation and temozolomide treatments(Stupp, Mason et al. 2005). Of particular interest is whether the survival experience of the two groups begins to diverge at the time that vaccine is administered 3-4 months after patient enrollment.

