1972) will be used to compare TTP and survival between the groups and with appropriate matched historical control groups. We would consider daclizumab worthy of further evaluation only if it did not significantly reduce TTP or overall survival relative to the control group and relative to the historical controls. Therefore, in the proposed study, we are interested in determining whether either treatment regimen is definitely worse than our best contemporaneous results at Duke University which are with the use of radiolabeled MABs delivered intratumorally. The most recent Phase II trial evaluating radiolabeled MABs at Duke in patients with newly-diagnosed GBM had a median survival of 79.4 weeks, and the lower limit of the 95% confidence interval was 61.4 weeks. Assuming that survival is exponential in this context, a median of 61.4 weeks translates into a 6-month survival of approximately 75%. Therefore if 6-month survival is not definitively <75%, there would remain interest in further development of the regimen proposed here. With 10 patients in each arm of our trial, one can conduct a test with  $\alpha=\beta=0.1$  to differentiate between a 6-month survival rate of 35% and 75%. That means that if the true 6-month survival rate were  $\leq 35\%$  there is <10% chance of concluding that the treatment regimen is worthy of pursuing with further investigation. Similarly, if the true 6-month survival rate were  $\geq 75\%$  or more there is  $\leq 10\%$  chance of rejecting the treatment. Other comparison groups that could be used include a historical control database, the recently published Phase III trial of the regimen of TMZ to be used in this trial, or our previous trial dataset using this vaccine approach which had median survivals (95% CI) of 14.7 (12.0, 17.4), 14.6 (10.9, 21.2), and >29.8 months, respectively. In addition, we will assess clinical efficacy by estimating the proportion of patients who survived longer than expected according to Curran's recursive partition analysis (Curran, Scott et al. 1993).

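### Sections 7.3, 7.4 and 10.3 treat the published cohort as having had this trial's temozolomide; the protocol does not support that after radiation, so temozolomide and vaccine effects on TTP and survival cannot be separated

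*Protocol*

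**What the plan says.** Section 7.3 plans an intent-to-treat comparison of TTP with that "experienced by a historical cohort of patients administered the same external beam radiation and temozolomide treatments", citing the published phase III trial of radiotherapy plus temozolomide. Section 7.4 repeats this for survival, with a "historical cohort of patients administered the same external beam radiation and temozolomide treatments". Both sections take particular interest in whether the curves separate when vaccine is given, 3-4 months after enrollment. Section 10.3 lists, among possible comparison groups, "the recently published Phase III trial of the regimen of TMZ to be used in this trial".

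On temozolomide after radiation, the protocol says:

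- **Comparator (section 3.15.2):** it refers to the "very limited dose density of maintenance temozolomide actually given" in that study and reports that "only 78% of patients started maintenance temozolomide, and only 47% of patients completed all 6 cycles". It adds that progression was the most frequent reason for stopping early and that the benefit of maintenance is unclear.
- **This trial, body text:** section 5.1.1 states "TMZ will be given on days 1-21 of a 28 day cycle". Section 5.2.1 states "a total of 6 additional cycles of TMZ (100 mg/m 2 /days 1-21) will be given". Section 5.1.3 agrees, and all three let the treating neuro-oncologist change the regimen.
- **This trial, elsewhere:** the synopsis recommends the 21-day regimen but also places the later cycles on days 1-5. The flow sheet gives days 1-5 for the initial and later cycles. Section 5.1.3 also mentions a five-day adjuvant course.
- **Cycle 2:** section 3.15.2 says its start is delayed by 1-3 weeks in all arms.

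**The concern.** The randomised contrast is daclizumab against saline, and every patient is vaccinated. A vaccine effect on TTP or survival can therefore be read only against an external cohort. That reading needs the cohort to have had comparable background treatment, and sections 7.3, 7.4 and 10.3 assert that it did. For the maintenance phase, which covers most of the TTP and survival follow-up, the protocol describes the comparator's temozolomide in one way and prescribes this trial's in another, and it is inconsistent about the latter.

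If the assertion stays, a better or worse result than the published cohort invites a conclusion about the vaccine that the data cannot support. The issue also reaches daclizumab. Section 2.2.2 makes progression-free survival against historical cohorts a secondary objective, and section 10.3 weighs daclizumab partly against historical controls.

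**Working it through.** The protocol gives no power or error rate for the comparison with this cohort, so there is no stated figure to reproduce. The check sets the passages side by side; the arithmetic is illustrative.

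**1. Is the post-radiation temozolomide the same?**

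| | Published cohort | This trial |
|---|---|---|
| Schedule | Not stated in the protocol | Days 1-21 of 28 at 100 mg/m2/d (5.1.1, 5.1.3, 5.2.1); days 1-5 (synopsis for later cycles; flow sheet) |
| Cycles | 78% started, 47% completed 6 (3.15.2) | 6 planned, cycle 2 delayed, regimen adjustable |

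From 78% and 47%, the comparator's mean number of cycles can be bounded by letting those who started but did not finish receive between 1 and 5 cycles.

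- If 47% is of all patients: 0.47 x 6 + 0.31 x 1 = 3.13, up to 0.47 x 6 + 0.31 x 5 = 4.37.
- If 47% is of starters (0.78 x 0.47 = 0.367 completing): 0.367 x 6 + 0.413 x 1 = 2.6, up to 0.367 x 6 + 0.413 x 5 = 4.3.

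The comparator therefore averaged about 2.6 to 4.4 of 6 cycles, or 44% to 73%. Delivery in this trial is not yet known.

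**2. Dose per cycle (illustration).** The body text targets 100 x 21 = 2,100 mg/m2 per cycle. Section 3.12 mentions a five-day regimen of 150-200 mg/m2, which is 750-1,000 mg/m2 per cycle. *Assuming* the comparator used that regimen, the ratio is 2,100/1,000 = 2.1 to 2.100/0.750 = 2.8. The protocol does not say that it did.

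**3. Can timing separate the two effects?** Section 5.2.1 gives vaccine #1 on day 21 ± 2 of the first post-radiation cycle, so temozolomide and vaccine start 19 to 23 days apart. Scans are every 8 ± 4 weeks (sections 5.2.1 and 6.2.4), so at least 28 days apart. For TTP, the gap is shorter than the shortest scan interval. For survival, an effect starting with the temozolomide cycle and one starting three weeks later would look alike with 20 patients.

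**4. What an unseparated effect could do (illustration).** Take an inert vaccine, 20 events, a fixed historical rate and a one-sided 0.05 test. With a temozolomide-only hazard ratio HR, the chance of declaring a gain is 1 - Φ(1.645 - √20 x ln(1/HR)).

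| Assumed HR | √20 x ln(1/HR) | Chance of a declared gain |
|---|---|---|
| 1.00 | 0 | 5% |
| 0.92 | 0.373 | 10% |
| 0.90 | 0.471 | 12% |
| 0.80 | 0.998 | 26% |
| 0.70 | 1.595 | 48% |

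The documents supply none of these hazard ratios. A hazard ratio above 1 would move the chance below 5% and could hide a real gain.

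**The case against.** Several points on the other side are sound.

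- **Status of the endpoints.** Section 10.3 says TTP is not primary and survival is not an endpoint; both serve to generate hypotheses. Section 7.4 promises careful interpretation. This limits the consequence. It does not correct a specific statement that the treatments were the same.
- **Role of section 10.3.** Its decision rule mainly asks whether a regimen is worse, the benchmark is radiolabelled antibody treatment, and the phase III trial is only a possible comparator. The section 2.1 hypothesis names a different, institutional cohort. A reader might infer that the plan rests a superiority claim for the vaccine on the published trial; section 10.3 does not do so. Sections 7.3 and 7.4 do plan the comparison and look for divergence at vaccination.
- **A narrower meaning.** In 7.3 and 7.4 the wording follows a mention of concurrent radiation and temozolomide, so it may mean that phase only. This is a fair reading of those two sections, but not of 10.3, which speaks of the regimen. On either reading, follow-up runs through maintenance.
- **Delivered against planned dosing.** Section 3.15.2 reports what the comparator's patients received, and progression was the usual reason for stopping. The same attrition can occur here. A reader might infer that the comparator was prescribed a weaker regimen, or that exposure here will be 2.1 to 2.8 times higher. The protocol shows neither.
- **If the schedule is reconciled to days 1-5.** The contrast with 21-day dosing then goes. The sameness wording would still be unsupported, because the comparator's schedule is not given, the regimen may be changed by the physician, and cycle 2 is delayed.

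**Conclusion.** The concern holds in limited form. The protocol does not support its statement that trial and comparator share a temozolomide regimen after radiation, and its own passages on this trial's schedule conflict. Because vaccine is common to both arms and starts about three weeks after post-radiation temozolomide, a difference from the published cohort cannot be assigned to either, and separation of the curves at vaccination does not identify the vaccine.

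Size and direction are unknown. A reader might infer that a temozolomide benefit will be credited to the vaccine; that presumes an effect which section 3.15.2 calls unclear. The 2.1-2.8 dose ratio assumes a comparator schedule the protocol does not state. The 10% to 48% figures assume hazard ratios and a test that is not planned (section 10.3 names Cox models), so they are not error rates of this trial.

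The primary endpoint and the randomised daclizumab comparison are unaffected. What changes is what may be concluded from the historical comparison, including the secondary objective on progression-free survival.

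**What to change.** 1. Reconcile the temozolomide schedule across the synopsis, sections 5.1.1, 5.1.3 and 5.2.1, and the flow sheet. No view is taken here on which schedule is right.
2. In 7.3 and 7.4, remove the statement that the cohort had the same temozolomide, or limit it to the concurrent radiation phase. In 10.3, remove the description of the phase III trial as one of this trial's regimen, or limit it likewise.
3. State in 7.3 and 7.4 that any difference from the published cohort is a combined temozolomide-plus-vaccine effect, and that divergence at vaccination will not be attributed to the vaccine.
4. Tabulate the temozolomide actually given, by patient and arm, as description only. Do not split the intent-to-treat comparison by delivered cycles or schedule. Patients who progress early receive fewer cycles, so the split would condition on the outcome, and the comparator's schedule is not available to match on.
5. Base daclizumab conclusions on TTP and survival on the randomised arms.

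The cost is wording and one table. The flow sheet has no temozolomide-dosing item, so collection of dosing data should be confirmed. The downside is that the historical comparison supports a weaker claim. Sample size and the primary analysis do not change.

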### **7.4 Survival**

Survival data in the context of this Phase I/II trial will be interpreted with great care. Still there are a few studies in the literature that may be able to be compared to our study to some degree given that they have similar patient populations. For example, the carmustine polymer study(Westphal, Hilt et al. 2003) and the TMZ study(Stupp, Mason et al. 2005), both have a set of very similar inclusion and eligibility criteria.

In addition, the authors of this study are also aware of the benefit of recursive partitioning analysis of prognostic factors in the comparison of different treatment strategies for patients with MG(Curran, Scott et al. 1993; Lamborn, Chang et al. 2004). Comparison with these studies will allow us to compare the results of the current clinical trial to previously published trials of patients with similar prognostic features.

An intent-to-treat analysis will be conducted to compare the survival experience of patients identified to receive vaccine treatment upon completion of concurrent external beam radiation and temozolomide assuming there was no intervening disease progression to that experienced by a historical cohort of patients administered the same external beam radiation and temozolomide treatments(Stupp, Mason et al. 2005). Of particular interest is whether the survival experience of the two groups begins to diverge at the time that vaccine is administered 3-4 months after patient enrollment.

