### **2.2.2      Secondary Objectives**

- To evaluate the safety of daclizumab in the context of vaccinating adult patients with newly-diagnosed high grade gliomas using CDX-110 during recovery from therapeutic TMZ-induced lymphopenia.
- To determine if daclizumab enhances the magnitude or character of CDX-110-induced cellular or humoral immune responses, inhibits or enhances activation-induced cell death, or induces immunologic or clinical evidence of autoimmunity.
- To determine if daclizumab alters the phenotype (CD56-expression), cytokine secretion profile, or cytotoxicity of CD3-CD56+ NK cells.
- To determine if daclizumab in addition to vaccination extends progression free survival compared to historical cohorts.
- To characterize immunologic cell infiltrate in recurrent tumors and seek evidence of antigen escape outgrowth.

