### **3.15.2 Standard of Care Regimen**

Data generated in a collaborative Phase III study performed by the RTOG and EORTC (Stupp, Mason et al. 2005) clearly suggested that the addition of adjuvant and maintenance TMZ to adjuvant radiation can prolong survival in patients with newly diagnosed GBM. These data served as the basis for FDA approval of TMZ for this indication (Cohen, Johnson et al. 2005). While this regimen has not been universally adopted in the clinic, primarily because the contribution of maintenance TMZ (given for 6 months following concurrent chemoradiation) is not defined, it is certainly recognized as a reasonable standard of care for patients and has been listed as such in the National Comprehensive Cancer Network Clinical Practice Guidelines for CNS cancers Version 1.2006 ([http://www.nccn.org/professionals/physician\\_gls/PDF/cns.pdf](http://www.nccn.org/professionals/physician_gls/PDF/cns.pdf)).

While it has been traditionally felt that chemotherapy would compromise the cellular elements necessary to generate immune responses, recent data suggest that perhaps chemotherapy can augment immune effects through either preferential elimination of regulatory components, or amplification of antigen exposure following cytotoxic cell damage. The possible synergy of vaccination in combination with conventional chemotherapy has been evaluated (Wheeler, Das et al. 2004; Heimberger, Hussain et al. 2006). In general, it appears that the immune system recovering from a cytotoxic insult may be hyperacute and particularly responsive due both to increased stimulatory

cytokines within the environment and reduced regulatory elements. Specific data have been generated testing the combination of vaccination with temozolomide and have shown that immune responses are not compromised(Heimberger, Sun et al. 2007).

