#### **4.1.2 Disease Status**

The patient must have a histopathologic diagnosis of a high grade glioma (WHO Grade III or IV) as confirmed by the study pathologist, [name], or his designate. The patient must undergo leukapheresis for immunologic monitoring.

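### WHO Grade III patients are eligible, but the chemoradiation cohort fixed for the TTP and survival comparisons, and the six-month survival benchmark, are glioblastoma series

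*Protocol*

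**What the plan says.** **Eligibility.** Section 4.1.2: "The patient must have a histopathologic diagnosis of a high grade glioma (WHO Grade III or IV) as confirmed by the study pathologist". The synopsis says the same.

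**Objective.** Section 2.2.2 lists as a secondary objective: "To determine if daclizumab in addition to vaccination extends progression free survival compared to historical cohorts".

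**Comparator.** Section 7.3 sets an intent-to-treat TTP comparison against "a historical cohort of patients administered the same external beam radiation and temozolomide treatments", citing the published chemoradiation trial. Section 7.4 repeats this for survival. Section 3.15.2 describes that trial's result as showing that "addition of adjuvant and maintenance TMZ to adjuvant radiation can prolong survival in patients with newly diagnosed GBM", and section 3.4.3 also lists it among trials in newly diagnosed GBM.

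**Claim of similarity.** Section 7.4 says of the carmustine and temozolomide studies that they "both have a set of very similar inclusion and eligibility criteria".

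**Benchmark.** In section 10.3 the six-month survival rule rests on a radiolabelled-antibody series "in patients with newly-diagnosed GBM had a median survival of 79.4 weeks", with a lower confidence limit of 61.4 weeks, converted to about 75% alive at six months. The rule is to separate 35% from 75% with 10 patients per arm and both error rates at 0.1.

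**Analysis set.** Sections 8 and 10.3 analyse clinical endpoints in all patients. The one stratified analysis described is by complete resection versus residual disease, not by grade.

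**The concern.** Taken as written, a group that may mix Grades III and IV is set against a Grade IV cohort, with nothing in 7.3 or 7.4 to restrict or adjust for grade. If Grade III carries a better prognosis, part of any apparent advantage is case mix, and its size depends on how many Grade III patients happen to enrol among about 20. Two uses of the data are exposed: the secondary progression-free survival objective, and the 10.3 judgement on whether the regimen deserves further work. In the second, better-prognosis patients could also hide harm.

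**Working it through.** **1. The plan's own figures.** With exponential survival and a median of 61.4 weeks, S(26 weeks) = exp(−ln 2 × 26/61.4) = 0.746, which agrees with the stated 75%. The protocol gives no cut-off for its rule. With n = 10, requiring at least 6 alive at six months gives alpha = P(X ≥ 6 | p = 0.35) = 0.095 and beta = P(X ≤ 5 | p = 0.75) = 0.078. Both are within 0.1, so the arithmetic is sound and the issue is the population.

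**2. Effect on medians with no treatment effect.**

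From the documents: GBM median survival m = 14.6 months (3.4.3 and 10.3) and median TTP m = 6.9 months (3.4.3), both for standard chemoradiation.

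Assumed, because the documents give neither: Grade III share g of 10%, 20% or 40%; Grade III median k times the GBM median, with k from 1.5 to 3; exponential times in each grade.

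The pooled median t solves

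(1 − g) × 2^(−t/m) + g × 2^(−t/(k·m)) = 0.5.

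Example with g = 0.2, k = 3, m = 14.6, t = 17.5: 0.8 × 2^(−17.5/14.6) + 0.2 × 2^(−17.5/43.8) = 0.349 + 0.152 = 0.50.

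| Grade III share | Median survival, months (k = 1.5 to 3) | Median TTP, months (k = 1.5 to 3) | Apparent gain |
|---|---|---|---|
| 0% | 14.6 | 6.9 | 0% |
| 10% | 15.2–15.9 | 7.2–7.5 | 4–9% |
| 20% | 15.8–17.5 | 7.4–8.3 | 8–20% |
| 40% | 17.1–21.6 | 8.1–10.2 | 17–48% |

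The bias is zero if no Grade III patient enrols or if k = 1.

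**3. Effect on the six-month rule.** Suppose GBM patients have the unacceptable 35% rate and Grade III patients an assumed 85–95%. The chance of at least 6 of 10 alive, which is 0.095 with no Grade III patient, becomes:

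- 0.154–0.166 with one Grade III patient in the arm
- 0.240–0.275 with two
- 0.355–0.428 with three

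**4. What restriction does to the same rule.** Exact binomial error rates with the Grade III patients left out:

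| Grade IV patients in arm | Cut-off (alive) | alpha | beta |
|---|---|---|---|
| 10 | ≥ 6 | 0.095 | 0.078 |
| 9 | ≥ 5 | 0.172 | 0.049 |
| 9 | ≥ 6 | 0.054 | 0.166 |
| 8 | ≥ 5 | 0.106 | 0.114 |
| 8 | ≥ 6 | 0.025 | 0.322 |

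No cut-off keeps both errors at or below 0.1 with nine or eight patients.

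**The case against.** **The protocol is cautious about these comparisons.** Section 7.4 promises careful interpretation and claims only partial comparability. Section 10.3 says that TTP is not a primary endpoint and survival not an endpoint, and 8.1.1 calls everything beyond the primary endpoint exploratory. This limits the weight of the point. It does not change which patients 7.3 and 7.4 compare.

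**Prognostic adjustment is mentioned.** Section 7.4 invokes recursive partitioning just before the intent-to-treat paragraph, each patient is assigned a prognosis, and the Cox comparison in 10.3 uses matched controls. These could offset part of the bias, and details of matching may properly sit in an analysis plan. But no matching factors are named, and neither device is tied to the comparison with the chemoradiation cohort.

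**Not every comparator is shown to be GBM.** This stands. The reference list titles the carmustine trial as one in primary malignant glioma, although 3.4.3 groups it with GBM trials. No histology is given for the 14.7-month historical database in 10.3 or for the matched cohort in 2.1.

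**Direction and size are uncertain.** This also stands. All patients must be EGFRvIII-positive, which section 3.3 links to treatment resistance; against comparators not described as so selected, that could push the other way. Section 3.3 also says the mutation is most frequent in GBM, so few Grade III patients may enrol. In simulation, the median of 20 uncensored exponential times with true median 14.6 months has a 95% range of about 7.5 to 25.6 months, so the 20% scenario is well inside chance variation. That makes the bias hard to see in the data; it does not remove it.

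**Other eligibility differences.** A reader might infer that the performance-status, steroid and multicentric-disease criteria also differ from the comparators. The documents do not give the comparators' criteria, so only the grade difference can be shown.

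**Conclusion.** The mismatch holds for the chemoradiation cohort in 7.3 and 7.4 and for the benchmark in 10.3. As regards grade, the similarity claim in 7.4 is not supported by how the protocol describes the temozolomide study.

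That the comparisons favour the regimen is conditional on Grade III patients having a better prognosis, which the documents do not quantify. Under the assumptions shown, the apparent gain runs from 4–9% at a 10% share to 17–48% at 40%; nothing in the documents supports a share as high as 40%.

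A reader might go further and conclude that every historical comparator is GBM, or that the trial's net bias against historical controls is certainly upward. The documents support neither: some cohorts have no stated histology or a broader label, and EGFRvIII selection may act in the opposite direction. The randomised daclizumab-versus-saline comparison and the primary T-Reg endpoint are untouched. The point merits correction but does not threaten the trial's main purpose.

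**What to change.** - **Sections 7.3 and 7.4:** restrict comparisons with the chemoradiation cohort, and with any other GBM-only cohort, to patients with histologically confirmed WHO Grade IV tumours. Report Grade III patients descriptively.
- **Section 7.4:** replace the similarity claim with a statement that this trial also admits Grade III. Do not list other differences unless the comparators' criteria are set out.
- **Section 10.3:** apply the 35%/75% benchmark to Grade IV patients, name the cut-off, and state the error rates at the actual Grade IV number per arm.

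Eligibility, treatment and the randomised analysis stay as they are. The changes to 7.3 and 7.4 are wording, at the price of slightly fewer patients in the historical comparisons. The change to 10.3 costs more: if one or two Grade III patients are left out of an arm of 10, the stated error rates of 0.1 and 0.1 no longer hold, and the protocol must either accept the rates shown above or change the rule or the accrual.
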